#### Health and social care professionals

*Focus groups*: up to 15 carers, and HSCPs (including GPs, geriatricians, clinical psychologists, psychiatrists, community psychiatric nurses, community nurses, physiotherapists, occupational therapists and music therapists) will be recruited through personal and professional networks including Royal College of General Practitioners, Clinical Research Networks, JDR, Alzheimer’s Society, Age UK and GMMH. HSCPs invited to participate in the study will be provided with a PIS and consent form in advance of their involvement in these events. The study information, including PIS and consent form, will be disseminated on our behalf by the professional organisations. HSCPs who are interested in the study will be advised to contact the researcher, and the researcher will answer any questions the participants may have. All participants will be requested to return the completed consent form if willing to participate within 48 hours if possible. A follow-up attempt will be made for participants who failed to respond within 48 hours; however, extensions can be provided on request to ensure everyone interested has an opportunity to participate.

### Additional recruitment strategy

As an additional strategy to supplement recruitment, the researcher will present information about the study at events organised by patient organisations and local carer groups across Greater Manchester to recruit both PLwD and carers. Participants who indicate an interest to take part in the study will complete a consent-to-contact form. Participants who expressed an interest will be contacted by the researcher via face-to-face or email or telephone as preferred to check eligibility, screen for capacity, discuss the study and answer any questions that participants may have. Assuming participants wish to continue with the study and meet the eligibility criteria, a face-to-face meeting will be arranged either at the participant’s home or a dementia café based on their preference and a time convenient to them. Participants will have 1 week to consider taking part in the study. A follow-up attempt will be made for participants who fail to respond within 1 week.

### Randomisation

After assessing for eligibility, baseline assessments and questionnaires will be undertaken and then participants will be randomly allocated to either receive the intervention (KOKU-LITE programme plus dementia-specific falls prevention leaflet) or control (dementia-specific falls prevention leaflet). Simple randomisation will be done using sealed envelopes^31^ (an online platform to perform randomisation). Randomisation will be performed by a researcher independent of the study. Participants will be informed of the randomisation via telephone, email or post. All participants will have an equal chance of being allocated either to the intervention group (KOKU-LITE programme) or control group (dementia-specific falls prevention leaflet).

### Intervention design

Comparator—a dementia-specific falls prevention leaflet.

The control group will receive a dementia-specific falls prevention leaflet.

#### Study intervention—KOKU-LITE programme

The intervention (KOKU-LITE) is a digital gamified strength and balance exercise programme with health literacy games (including home hazard, hydration, nutrition, bone and brain health education). The programme is automatically tailored to the individual needs of each participant. Prior to using KOKU-LITE, participants are advised to complete a prescreening questionnaire (figure 2). Based on their responses, they will be directed to a set of exercises (figure 3) that are appropriately tailored to their functional ability. The exercise regimen begins with simple and low-intensity exercises and progresses gradually to more complex exercises. All exercises are underpinned by the evidence-based principles of FaME-OTAGO strength and balance exercise programmes.

**Figure 2 F2:**
[figure not shown]
Prescreening questionnaire presented to participants. Participants will be instructed to select an option from the list that best describes them to determine their eligibility for the study.

**Figure 3 F3:**
[figure not shown]
A screen with a set of tailored exercises presented to participants.

Participants will attend a KOKU-LITE group training session lasting for 60 min. Group sizes may vary between two and four participants, depending on time availability and allocation requirements. A carer may also accompany the participant if they feels their support would be beneficial. An iPad will be provided to participants for the duration of the project and the app instruction booklet will also be provided for reference purposes. For participants who do not wish to attend the group training, ad hoc one-to-one training will be offered.

Participants will be advised to use the modified KOKU-LITE programme for 30 min, 3 times per week, for 6 weeks in their own homes. While we recommend participants to adhere to this dosage, as this is a feasibility study, our primary aim is to assess whether participants are able to follow and adhere to the programme. Evaluating the effectiveness of the intervention will not be the focus of the study at this stage. According to current public health guidelines, it is recommended to engage in moderate to vigorous physical activity for a minimum of 30 min, 3–5 times per week, to promote optimal physical and mental health.^32 33^ Participants will have the flexibility to choose their days and time they use the app, based on their individual needs. Additionally, participants will be encouraged to read and use the dementia falls prevention leaflet alongside the KOKU-LITE app.

During the intervention, the researcher will carry out a weekly visit to participants (either at participants’ home or a dementia café (dementia café is a café that offers a supportive and welcoming space to socialise, learn more about dementia and access helpful resources, information and local services)) based on participants’ preferences to provide support (if required). Additional training on how to use the iPad will be provided in addition to the app training session. During the home visits, researchers will offer personalised support to each participant to ensure adherence to the intervention. Adherence will be monitored through the app’s performance tab (figure 2), which tracks progress and allows for timely adjustments as necessary.

If participants do not adhere to the programme, the following strategies will be implemented:

We will investigate the underlying reasons for non-adherence and address these challenges during home visits. In addition, participants will receive weekly phone calls to provide reminders and encourage them to complete the exercises and engage with the games.Based on the identified reasons for non-adherence, we will make appropriate adjustments and arrangements to better support the continued use of the app.

In between the sessions, participants will be advised to contact the research team or dementia support advisors (who organise the cafés) if they experience any difficulties using the app. Contact details of the research team will be provided to the participants.

### Patient and public involvement

KOKU is a tablet/iPad-based digital gamified strength and balance exercise programme, specifically co-designed with older people for older people at risk of falls.^23^ Following Medical Research Council complex intervention guidance,^34^ we have engaged with PLwD and carers of PLwD and co-developed KOKU to suit the needs of PLwD to make it dementia-friendly and more accessible by simplifying the language and other features (online supplemental appendix 4). This version is known as KOKU-LITE. This current project continues the involvement of PLwD and carers of PLwD in feasibility testing of KOKU-LITE to inform a larger study that will test effectiveness.

We have formed a project advisory group from the outset for this study. Project advisory group members have lived experiences, either as a person living with dementia or caring for someone with dementia. Project advisory group members will provide support to the research team throughout the study and with interpretation and dissemination of the findings. Patient and public involvement will be critical and form an integral part of the project to ensure the project discussions are informed by patients’ and carers’ voices. We will explore the support needed for the participants in terms of feasibility and accessibility of the meetings and documentation for the project including protocol, flyers, PIS, consent forms, etc. The group will continuously provide feedback on documents and meet regularly (at least once a month) to support and provide direction to the research.

### Outcome assessment

#### Primary outcomes

The feasibility and acceptability of the intervention will be evaluated in terms of recruitment, retention and adherence rates throughout the trial (table 1). Where possible, reasons underlying these rates will be documented.

**Table 1 T1:** Criteria for progressing to a larger trial

Feasibility	Go—proceed with RCT	Amend—proceed with changes	No go—do not proceed with RCT
Participant recruitment	N≥70 participants consent to the study	N=36–69 participants consent to the study	N≤35 participants consent to the study
Retention rate	≥75% remain in the study (ie, have not withdrawn)*	51%–74% remain in the study (ie, have not withdrawn)	≤50% remain in the study (ie, have not withdrawn)
Data collection	Target: ≥85% of participants from the study have all the study data collected	51%–84% of participants from the study have the study data collected	≤50% of participants from the study have the study data collected
Acceptability			
Engagement and acceptability	≥75% participants used KOKU-LITE intervention	51%–74% participants used KOKU-LITE intervention	≤50% participants used KOKU-LITE intervention

* Retention rate will be ≥75%, considering the patient population.

KOKU, Keep On Keep Up; RCT, randomised controlled trial.

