**Methods and analysis:**

A two-arm, parallel, non-blinded feasibility randomised controlled trial will be conducted using mixed methods. Participants aged ≥55 years with any type but varying levels of dementia from mild to moderate stages (ratings 1 and 2 on clinical dementia rating (CDR) scale) and meeting the eligibility criteria will be recruited from patient organisations across Greater Manchester, UK. The target sample size is 60 for the trial. Participants randomised into the intervention arm will use the KOKU-LITE programme for 30 min, 3 times a week for 6 weeks plus dementia-specific falls prevention leaflet and participants randomised into the control arm will receive dementia-specific falls prevention leaflet. Outcome measures: primary outcomes: recruitment, retention and adherence rates; secondary outcomes: quality of life, participants’ activities of daily living, physical activity levels, functional ability, lower limb strength, concerns about falling, falls risk, mood and user’s experience of the technology. Post-intervention interviews or focus groups with participants and health and social care professionals will explore the feasibility of trial processes and technology and evaluate the usability and acceptability of the intervention, respectively. Analyses will be descriptive.

Trial status: the first participants were recruited on 20 March 2024. Data collection is currently ongoing.

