### Study participants

As this is a feasibility study, we aim to recruit up to 60 participants (PLwD) (with any type but varying levels of dementia from early diagnosis (mild stages) to moderate stages of dementia (with ratings 1 and 2 on CDR scale) (30 participants in each group) to test the feasibility, usability and acceptability of KOKU-LITE, feasibility of the recruitment processes and suitability of the outcome measures. Up to 15 carers and HSCPs (including general practitioners (GPs), geriatricians, clinical psychologists, psychiatrists, community psychiatric nurses, physiotherapists, occupational therapists, community nurses, occupational therapists and music therapists) (or until saturation) will be recruited to evaluate the usability and acceptability of the app for this target population.

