### Recruitment

#### People living with dementia

*Intervention study*: up to 60 participants (PLwD) (with varying levels of dementia from early diagnosis (mild stages) to moderate stages of dementia) will be recruited. The CDR scale will be used to screen PLwD.^30^ We will work with professional organisations across Greater Manchester, including Dementia United (DU) (DU is Greater Manchester Integrated Care’s programme for dementia), Join Dementia Research (JDR), African Caribbean Care Group, Together Dementia Support, Alzheimer’s Society and Age UK to identify PLwD who are willing and able to participate in the study. The study information, including leaflets and participant information sheet (PIS), will be disseminated on our behalf by DU (established collaboration from previous work), Greater Manchester Mental Health NHS Foundation Trust (GMMH), Age UK, Dementia UK and other patient organisations to their members and the populations that they serve across Greater Manchester.

In addition, we will use snowball sampling (ie, participants will be asked to forward the study leaflet and the PIS to individuals they know who have the same condition) to advertise the study and extend our recruitment to individuals who might not be engaged with third sector organisations. Different formats of the PIS will be prepared (if needed) to accommodate the needs of PLwD. For example, different font sizes and background colours will be used with PIS. Audible versions of the PIS will be provided when required. Participants interested in the study will be advised to contact the research team directly or via their carer (via email) if they are willing to take part in the study. Participants who indicate an interest will then be contacted by the researcher via face-to-face to discuss the study, check eligibility, screen for capacity and answer any questions that participants may have. Assuming participants wish to continue with the study and meet the eligibility criteria, a face-to-face meeting will be arranged either at the participant’s home or a dementia café based on their preference and a time convenient to them. Participants will be sent consent forms (onlinesupplemental appendix 3.1  3.2) in advance of the researcher meeting the them, to ensure they have the opportunity to read the forms and ask any questions. Consent forms will be completed at the participant’s home or at a dementia café based on their convenience.

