### Sample size

The total sample size for this study is 75 (60 PLwD for the feasibility study and 15 HSCPs for the interviews).

The intended sample size for the feasibility study will be 30 PLwD in each group, in which simple randomisation will be used with a 1:1 allocation. An attrition rate of 10%–20% is reasonable. A formal sample size calculation is not required as this study focuses on the practicalities of conducting the study. This number is pragmatic to assess the feasibility of the KOKU-LITE programme with the outcome measurements. It is anticipated that this sample size will provide sufficient information to inform a future definitive trial, assuming that the KOKU-LITE programme proves feasible and acceptable for PLwD.^35^

Up to 15 carers and HSCPs (including GPs, geriatricians, clinical psychologists, psychiatrists, community psychiatric nurses, community nurses, physiotherapists, occupational therapists and music therapists) will be recruited to evaluate the usability and acceptability of the app for this target population.

Feasibility of the KOKU-LITE intervention will be assessed based on the feasibility criteria outlined in table 1.^35^,^38^

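### Table 1 sets the recruitment Go threshold at 70 consents, but the trial plans at most 60 people with dementia, so full recruitment is graded Amend

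*Protocol article*

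**What the plan says.** Recruitment is one of the primary outcomes, and the Sample size section says that feasibility will be judged by Table 1. The recruitment row of that table has three cells:

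- Go: "N≥70 participants consent to the study"
- Amend: "N=36–69 participants consent to the study"
- No go: "N≤35 participants consent to the study"

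The planned size is given in four other places:

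- Study participants: "we aim to recruit up to 60 participants (PLwD", with 30 in each group.
- Recruitment, People living with dementia: "up to 60 participants (PLwD) (with varying levels of dementia from early diagnosis (mild stages) to moderate stages of dementia) will be recruited".
- Abstract, Methods and analysis: "The target sample size is 60 for the trial".
- Sample size: "The intended sample size for the feasibility study will be 30 PLwD in each group", within a whole-study total of 75 made up of "60 PLwD for the feasibility study and 15 HSCPs for the interviews".

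The first two state a ceiling. The Abstract gives a target and the Sample size section an intended size. All four give the same number.

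**The concern.** A progression rule should be able to return each of its verdicts for the trial as designed. Here the top verdict requires more people than the design allows, so a team that recruits everyone it planned to recruit would report that recruitment needs changes. Recruitment is a primary outcome, and the Analysis section makes use of the summary statistics for sizing the definitive trial depend on the progression criteria being met. The label will therefore be read as evidence on whether a definitive trial can recruit.

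The lower edge does not fit the planned size either. The retention, data collection and engagement rows all place No go at 50% or below, and 35 is more than half of 60.

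**Working it through.** **Inputs.** Table 1 cut-points: 35, 36, 69 and 70. Planned number of people with dementia: 30 per group in two groups. Professionals in the whole-study total: 15. Attrition regarded as reasonable in the Sample size section: 10%–20%.

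**Step 1: reproduce the plan's totals.** 2 × 30 = 60 and 60 + 15 = 75. Both agree with the Sample size section. No power formula applies, because the plan states that no formal calculation is needed.

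**Step 2: grade full recruitment.** The maximum is 60. Since 36 ≤ 60 ≤ 69, the grade is Amend. The shortfall from Go is 70 − 60 = 10, and the Go threshold is 70/60 = 116.7% of the maximum.

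**Step 3: express the cut-points as shares of the possible bases.**

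| Base | 35/base | 36/base | 70/base |
|---|---|---|---|
| 60 | 58.3% | 60.0% | 116.7% |
| 70 | 50.0% | 51.4% | 100% |
| 75 | 46.7% | 48.0% | 93.3% |

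Only a base of 70 gives the 50%/51% boundary used in the other rows. On the base of 60, totals of 31 to 35 (31/60 = 51.7% to 35/60 = 58.3%) are No go in this row, while the same percentages are Amend in every other row.

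**Step 4: could attrition explain 70?** Inflating 60 gives 60/0.90 = 66.7 (67), 60/0.85 = 70.6 (71) and 60/0.80 = 75. None of these is 70, and the plan applies no inflation. It gives 60 as the number recruited, which leaves 60 × 0.90 = 54 to 60 × 0.80 = 48 after attrition.

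**Step 5: could consents exceed the number randomised?** Seventy consents for 60 randomised needs a loss of 10/70 = 14.3% between consent and allocation.

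**Step 6: rescale to 60.** Using 50% and 100%, the fractions that the row has on a base of 70: 0.50 × 60 = 30, so No go ≤30, Amend 31–59, Go 60.

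**The case against.** The strongest reply is that the row does not say who is counted, so Go may be reachable after all. There are two versions.

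*Counting professionals and carers.* The article calls them participants, they return consent forms, and its first objective covers recruitment of all three groups. With a whole-study total of 75, a count of 70 is possible. But the table decides whether to proceed to a randomised trial, and only people with dementia are randomised; the carers and professionals attend focus groups. On this count, 55 people with dementia plus 15 others would score Go, so the row would no longer measure recruitment to the trial. Nor do the cut-points fit 75.

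*Counting consents before randomisation.* Baseline assessments come before allocation, so some people could consent and never be randomised. But the Recruitment section checks eligibility before the meeting at which consent is completed, the ceiling applies to people recruited, and the 14.3% loss required is planned nowhere. The 10%–20% attrition is not tied to that stage.

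What stands is that the count is undefined, so the conclusion must be conditional on it.

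Three stronger readings are tempting and should be resisted:

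- A reader might infer that the chance of Go is flatly zero. That holds only if the row counts people with dementia recruited.
- A reader might infer that the cut-points were carried over from a target of 70. The fit is exact, but no section states such a target.
- A reader might infer that a fully recruited trial would be stopped. It would not, because Amend permits progression with changes.

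**Conclusion.** The recruitment row is wrong as written and has to be reconciled with the planned size. On the plain reading, that the row counts people with dementia recruited to the trial and that the ceiling of 60 is kept, Go is unreachable by 10 people and complete recruitment is graded Amend. The No go cut lies at 58.3% of the planned number, against 50% or less in the other three rows. This second misfit is a departure from the table's own pattern; the plan does not say that all rows must share one fraction.

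For a trial that fills, the consequence is a wrong label and a top band that cannot be used. The main contradiction needs only that 60 is less than 70, and does not depend on how the number 70 arose.

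**What to change.** 1. State in Table 1 that the row counts people living with dementia who consent to the randomised trial.
2. Reset the cut-points to the target of 60 by one stated rule. Keeping the row's apparent fractions gives No go ≤30, Amend 31–59, Go 60. This makes Go attainable only at exactly 100%, so 59 would be Amend. If the team prefers a lower Go fraction, it should choose one value and justify it. The choice matters: 75%, as in the retention and engagement rows, would be 0.75 × 60 = 45, and any total from 45 to 59 would then change from Amend to Go.
3. Make the change in a dated amendment that gives the consent count on that date, and report recruitment against both the published and the revised thresholds. Recruitment opened in March 2024 and the trial is unblinded, so the team can see the count as it accrues. A threshold lowered without that disclosure could look driven by the data.

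The cost is one table row, a protocol amendment and one extra reported comparison. No extra patients are needed.

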**Trial registration number:**

NCT06149702.

STRENGTHS AND LIMITATIONS OF THIS STUDYThis is one of the first studies to test the feasibility and acceptability of trial processes and usability of a gamified digital health application for strength and balance training to reduce falls, functional decline and to improve well-being in people living with dementia in the community (known as KOKU-LITE).Recruiting and retaining people living with dementia can be very challenging and therefore this feasibility study will explore and evaluate different strategies to recruit participants and estimate the time required for recruitment.The barriers and facilitators identified in the recruitment and retention phase of the trial will help us to design a robust definitive trial.We have involved people with lived experience of dementia extensively in the development of KOKU-LITE and will continue to do so in feasibility testing of KOKU-LITE to inform a larger study that will test effectiveness.This feasibility trial is not powered to determine the effectiveness of the intervention.

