**Figure 1 F1:**
[figure not shown]
Consolidated Standards of Reporting Trials (CONSORT) flow chart of Keep On Keep Up (KOKU)-LITE feasibility trial. The flow chart demonstrates the participants’ journey from enrolment to follow-up period. HSCP, health and social care professional; PLwD, people living with dementia.

A purposive sample of participants who have consented to take part in the study will be invited to participate in postintervention interviews. Exploratory data obtained from the interviews will increase understanding of the responses in the questionnaires about the usability and motivation to use KOKU-LITE, and feasibility of recruitment, data collection approaches and completion of outcome measures.

Patient recruitment has commenced in March 2024 and data collection will be completed by September 2025. The study will be reported in accordance with the Standard Protocol Items: Recommendations for Interventional Trials 2012 Statement for protocols of clinical trials^28^ (online supplemental appendix 1) and TIDieR checklist for the description of the intervention (online supplemental appendix 2). The study process is outlined in figure 1.

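### The Table 1 progression rule for recruitment counts consents over no stated period, so the Go/Amend/No go decision ignores the speed of recruitment, although the primary outcome is a recruitment rate

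*Protocol article*

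**What the plan says.** The Abstract (Methods and analysis) lists "primary outcomes: recruitment, retention and adherence rates". The Primary outcomes section repeats that feasibility and acceptability will be "evaluated in terms of recruitment, retention and adherence rates throughout the trial" and points to Table 1 for the criteria.

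The recruitment row of Table 1 has three bands:
- Go: "N≥70 participants consent to the study"
- Amend: "N=36–69 participants consent to the study"
- No go: "N≤35 participants consent to the study"

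The row gives no period. The other three rows (retention, data collection, engagement) are percentages.

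The strengths and limitations list says the study will "explore and evaluate different strategies to recruit participants and estimate the time required for recruitment". The Study participants and Recruitment sections both plan for up to 60 people with dementia, and the Sample size section sets 30 per group.

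On dates, the Abstract puts the first recruitment at 20 March 2024. The text under Figure 1 adds: "Patient recruitment has commenced in March 2024 and data collection will be completed by September 2025". Follow-up is 6 weeks (Study design). The article gives no closing date for recruitment.

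**The concern.** A rate needs a unit of time or a denominator, and the recruitment row has neither. A count of consents depends on two things: how fast people join and how long the door stays open. With a planned maximum of 60, a trial that fills tells the reader nothing further through the count; only the time taken to fill does.

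The sponsor of a definitive trial needs to know how many people per month this catchment and these recruitment routes can supply. The protocol recognises this when it sets out to estimate recruitment time, but that estimate plays no part in the Go/Amend/No go decision. A slow trial and a fast one can receive the same verdict on a primary outcome.

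This is a fault in a rule that the article itself fixes, not a detail left to an analysis plan. It also does not depend on the level of the cut-offs: moving Go to 60 would still give the same verdict to a quick trial and a slow one.

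**Working it through.** **Inputs from the protocol article.** First recruitment 20 March 2024 (Abstract). Data collection complete by September 2025 (text under Figure 1). Follow-up 6 weeks (Study design). Up to 60 participants, 30 per group (Study participants, Sample size). Bands of at least 70, 36 to 69, and at most 35 consents (Table 1).

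**The plan's own figures.** 2 × 30 = 60, and 60 + 15 professionals = 75. Both reproduce. The size is pragmatic, so there is no power calculation to check.

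**Inferred entry window.** The last useful entry is 6 weeks (42 days) before data collection ends. Taking a month as 30.4375 days:
- end on 1 September 2025: (530 − 42) / 30.4375 = 16.03 months
- end on 30 September 2025: (559 − 42) / 30.4375 = 16.99 months

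The window is therefore about 16 to 17 months. It is inferred here, not stated in the article.

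**Table 1 counts as monthly rates** (count / months):

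| Consents | Table 1 band | Per month, 16.03 months | Per month, 16.99 months |
|---|---|---|---|
| 35 | No go, upper limit | 2.18 | 2.06 |
| 36 | Amend, lower limit | 2.25 | 2.12 |
| 60 | Amend (planned maximum) | 3.74 | 3.53 |
| 69 | Amend, upper limit | 4.30 | 4.06 |
| 70 | Go, lower limit | 4.37 | 4.12 |

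**Same count, different speed.** The durations are assumed; the verdict is Amend in every case:
- 60 / 6 = 10.0 per month
- 60 / 12 = 5.0 per month
- 60 / 17 = 3.5 per month

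The first and last differ by a factor of 17 / 6 = 2.8. At those speeds, each 100 participants of a later trial from the same catchment would take 100 / 10 = 10 months or 100 / 3.53 = 28 months. The factor of 2.8 holds whatever size the later trial has.

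**Effect of time alone.** At a constant 2.0 per month, 17 months gives 34 consents (No go) and 18 months gives 36 (Amend). The band changes although the rate does not.

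**Which form of rate separates fast from slow.** Dividing both the bands and the observed count by the planned 17 months only rescales the count: 60 / 17 = 3.5 however quickly the 60 were reached. Dividing the observed count by the months actually open gives 10.0 for the 6-month case, above a Go level of 4.1 to 4.4, and 3.5 for the 17-month case, below it. On that rule, 60 consents reach Go if they are obtained within 60 / 4.37 = 13.7 to 60 / 4.12 = 14.6 months.

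**Go level against target.** 70 − 60 = 10, and 10 / 60 = 17% above planned recruitment.

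**The case against.** The strongest reply is that the period is nearly fixed elsewhere. With a stated start, a 6-week follow-up and a stated end of data collection, entry can last only about 16 to 17 months, and a count over a fixed period is a rate times a constant. No text provides for an extension. With at most 60 recruited, extra time could lift the trial from No go to Amend but never to Go. This bounds the problem. It does not remove it: Table 1 is tied to neither date, no recruitment closing date is given, and a trial that fills early scores no better than one that fills at the end.

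A reader might infer that the recruitment outcome cannot inform the next trial. The documents do not support that. A monthly rate can be computed from the dates, the study says it will estimate recruitment time, and reasons behind the rates are to be documented where possible. The weakness lies in the decision rule, not in everything that can be reported.

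A reader might also fault the absence of a denominator of people approached. That does not stand as a fault. Leaflets go out through third-party organisations and by snowballing, so the number reached is inherently unknown. Screening counts are commonly left to the full protocol or to the flow chart, which is not shown.

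Finally, recruitment is already under way, and the Protocol amendments section requires modifications to go to the sponsor and the ethics committee. That is a real cost.

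**Conclusion.** The concern holds in a limited form. The progression rule for a primary outcome named as a rate uses a count tied to no period, so the decision ignores speed. Sixty consents at 10 per month and sixty at 3.5 per month, a 2.8-fold difference, both come out as Amend. The rate can still be reported separately, so the information is not lost; it is left out of the decision.

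This rests on two assumptions. The entry window of 16 to 17 months is inferred from the stated dates. The planned maximum of 60 is read as limiting consents; if more people may consent than are randomised, the article does not say so. The 6-month and 17-month durations are illustrations, not forecasts.

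The change is worth making but does not threaten the conduct of the trial.

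**What to change.** Rewrite the recruitment row of Table 1 as follows.

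1. State the planned recruitment window: opening date, closing date and months.
2. Set each band as its count divided by the planned months. On the inferred window, No go becomes at most about 2.1 to 2.2 consents per month and Go at least about 4.1 to 4.4, with Amend covering everything between so that no gap is left on a continuous scale.
3. Compute the observed rate as consents divided by the months actually open to recruitment, ending when the target is reached or recruitment closes. Without this step the rate only rescales the count.
4. Keep consents as the numerator. If participants randomised are used instead, say so, because that number cannot exceed consents and the rule may become stricter.
5. Reconcile the bands with the target of 60, because a Go level of 70 consents exceeds planned recruitment.
6. Report consents among those found eligible beside the rate, as description only. The Recruitment and Additional recruitment strategy sections already have the researcher check eligibility.

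The wording and data costs are small: one table row, using consent dates that arise in the existing steps. The procedural cost is larger: an amendment to a progression criterion while recruitment is under way, which should be dated and reported as such. A slow start could also no longer be offset by recruiting for longer.
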